## Abstract

**Background:**

Novel strategies to limit the size of infarction and prevent adverse remodeling and heart failure in patients following acute ST-segment elevation myocardial infarction (STEMI) are lacking. Supersaturated oxygen (SSO_2_) therapy is approved for patients presenting within 6 h of onset of anterior STEMI using femoral artery access. The feasibility of SSO_2_ therapy via radial access is unknown. A more detailed understanding of the effect of therapy is needed.

**Objectives:**

To assess the primary outcome, defined as the within-participant change in the plasma concentration of NT-proBNP measured at baseline, 24 h, 2–5 days and 3-months post-MI.

**Design:**

Prospective, randomized, controlled, blinded, endpoint (mechanistic, PROBE) clinical trial.

**Randomized, controlled trial:**

After primary PCI, eligible participants will be blinded and randomized 2:1 to either 1 h of SSO_2_ therapy using radial artery access and intravenous glycoprotein IIbIIIa inhibitor therapy or a control (sham) procedure involving wrist manipulation in addition to standard care. The primary outcome is the within-participant change in the plasma concentration of NT-proBNP as detailed above. Secondary outcome assessments include coronary microcirculatory function, infarct size, microvascular obstruction, myocardial hemorrhage, left ventricular remodeling, myocardial blood flow, quality of life (EQ-5D-5L), Kansas City Cardiomyopathy Questionnaire (KCCQ) and the Duke Activity Status Index. Patient reported experience measures (PREMS) are an exploratory outcome. Health and economic outcomes will be assessed using electronic healthcare records.

**Value:**

The study will test the feasibility of radial artery access, provide mechanistic data and inform a larger multicenter trial powered to detect treatment effects on clinical endpoints.

Clinicaltrials.gov: NCT06662890

## Background

1

Acute ST-segment elevation myocardial infarction (STEMI) leads to transmural myocardial infarction, left ventricular systolic dysfunction and adverse left ventricular remodeling. The duration of myocardial ischemia, quantified as being the time from symptom onset to reperfusion, correlates with the size of infarction and the potential for myocardial salvage [1,2]. When the ischemic time extends beyond 6 h, the percentage of salvaged myocardium reduces such that the size of infarction may approximate the volume of jeopardized myocardium (area-at-risk) [1].

Supersaturated oxygen (SSO_2_) is a novel therapy to enhance myocardial salvage and limit infarct size [3]. SSO_2_ involves an extracorporeal circuit including an oxygen chamber that increases the achieved partial pressure of oxygen (PO_2;_ normal 75–100 mmHg) to between 760 and 1000 mmHg. Hyperoxygenated blood is returned into the left main coronary artery and hence the ischemic myocardium supplied by the infarct-related artery using a standard coronary catheter. Prior studies have involved femoral artery access. Theoretically, hyperoxygenated blood should be provided immediately to enhance salvage of ischemic myocardium [4]. The duration of effect on myocardial metabolism and translation to recovery of contractile function are less well established.

In the Acute Myocardial Infarction With Hypoxemic Therapy (AMIHOT)-1 (*n* = 269 including 105 participants with anterior STEMI, symptoms ≤6 h duration) and AMIHOT-2 (*n* = 301 participants) randomized, controlled clinical trials, SSO_2_ therapy via femoral artery access for 1 h after primary percutaneous coronary intervention (PCI) for anterior STEMI was shown to reduce the size of infarction as assessed using Tc-99 m-sestamibi single-photon emission computed tomography (SPECT) imaging [4]. In AMIHOT-2, among 281 randomized patients with cardiac SPECT imaging at 14-days post-MI, the median (interquartile range) infarct size was 26.5 % (8.5 %, 44 %) in the control group compared with 20 % (6 %, 37 %) after SSO_2_ therapy. The pooled adjusted infarct size was 25 % (7 %, 42 %) in controls compared with 18.5 % (3.5 %, 34.5 %) after SSO_2_ therapy (*p* = 0.02; Bayesian posterior probability of superiority, 96.9 %). Thirty-day rates of major adverse cardiovascular events (MACE) in the SSO_2_ group were noninferior to the control group [5].

Observational studies have added clinical evidence for the safety of the therapy using femoral artery access [6,7]. ZOLL Circulation Inc. have received FDA and CE Mark approval for SSO_2_ therapy in patients presenting with anterior STEMI within 6 h after symptom onset. However, adoption of this therapy is limited by the design for use of femoral artery access. Furthermore, there are no data on the effects of SSO_2_ therapy on coronary microvascular function, microvascular obstruction, intramyocardial hemorrhage or left ventricular remodeling, or in patients treated with a contemporary P2Y12 inhibitor, such as prasugrel. There are no data for procedures using radial artery access, as is recommended in guidelines for primary PCI, for the extracorporeal circuit, and no data from randomized, controlled trials involving this approach, and despite the results of the AMIHOT-2 trial, SSO2 therapy is not mentioned in contemporary guidelines.

### Rationale

1.1

Anterior STEMI is a life-threatening emergency associated with large infarction and a consequent risk of heart failure. Timely reperfusion with primary PCI is the standard of care for STEMI [8] but development of new therapies to limit the size of infarction, reduce the risk of adverse remodeling and prevent heart failure has proved challenging. No new effective therapy has been licensed for use after myocardial infarction since eplerenone twenty years ago [9]. Recent clinical trials of adjunctive reperfusion therapies (including a trial of intracoronary alteplase) have proved ineffective [[10], [11], [12]]. In response, novel approaches are being investigated, including device-based therapy [13] and intra-coronary cooling [14].

SSO_2_ therapy has shown promise in the AMIHOT trials [4,5] and the therapy is approved for use in patients with anterior STEMI within 6 h of onset of symptoms. Currently, however, the extracorporeal circuit for SSO_2_ therapy is made using femoral arterial access. However, radial artery access is recommended in clinical guidelines [8], with evidence for both reduced access site bleeding and mortality [15,16].

The study has two main objectives. The first objective is to provide preliminary evidence of efficacy for radial-based SSO₂ therapy post-MI and the second objective is to assess feasibility. Specifically, our primary clinical/physiological outcome measure is NT-proBNP, while the primary feasibility objective is to determine whether radial-based SSO₂ is achievable and safe without major bleeding or vascular complications. Secondary aims include, first, to undertake a detailed mechanistic evaluation of the effects of SSO_2_ therapy, using a combination of validated surrogate biomarkers, intracoronary physiology, and cardiovascular magnetic resonance imaging and, finally, to assess patient reported outcome measures (PROMS) and patient reported experiences measures (PREMS).

## Methods

2

### Study design

2.1

This is a prospective, randomized, controlled, blinded, endpoint (mechanistic, PROBE) clinical trial. The study design was informed by patient and public involvement at the NHS Golden Jubilee hospital and the research ethics service.

The rationale is to generate novel clinical data for supersaturated O_2_ therapy using exclusively radial artery access including feasibility (Table 1) and the effects on cardiac biomarkers using a randomized, controlled trial with measures to mitigate bias, including blinding with a sham experience, and blinded outcome assessments (Table 1). Therefore, the aims are for study participants, attending clinicians and outcome assessors to be blind to treatment group assignment. The effectiveness of blinding will be prospectively assessed.

**Table 1 t0005:** Secondary study objectives.

Objective	Methodology
Feasibility defined as a completed SSO2 therapy	Study design
Coronary angiogram at the end of supersaturated O2 therapy	Assessment of TIMI Coronary Flow Grade, angiographic Blush Grade, Frame Count and Thrombus Grade
ECG	Assess % ST-segment resolution on the 12- lead ECG (pre- vs. end of supersaturated O2 therapy 60 min post-reperfusion with primary PCI)
Coronary microvascular function	Assess measures of culprit artery microvascular function including the index of microvascular resistance (IMR), vasodilator capacity reflected by coronary flow reserve (CFR), resistance reserve ratio (RRR) and microvascular resistance reserve (MRR) before and after supersaturated O2 therapy, or sham control to permit between group comparisons.
Infarct characteristics	Assess myocardial infarct characteristics including infarct size, microvascular obstruction, myocardial hemorrhage, and myocardial salvage using CMR imaging 2–5 days and 3 months post-MI.
Left ventricular remodeling	Assess LV ejection fraction and LV remodeling, including LV end-systolic volume index and end-diastolic volume index, over 3 months using CMR imaging. Assess remote zone characteristics including native T1 (ms) and extracellular volume
Myocardial blood flow	Assess blood flow within myocardial segments subtended by the infarct-related artery at 3 months using stress CMR imaging.
Biomarkers	Assessment of circulating biomarkers over time (baseline (before coronary angiogram, pre-PCI, pre-randomization, pre-SSO_2_), 75 min (post-SSO_2_), 24 h ± 4 h, 2–5 days and at 3 months).
Health status	Assess health-related quality of life using patient reported outcome measures during follow-up, including the EQ-5D-5L, Duke Activity Status Index and Kansas City Cardiomyopathy questionnaires
Feasibility	Feasibility will be reflected by enrolment rates, procedure completion, adverse events, and patient reported experiences measures (PREMS) using a customized questionnaire.
Safety	Assessment of peri-procedural and post-procedural events as well as those during follow-up
Clinical outcomes	Assessment of clinical outcomes over 12 months and longer-term follow-up including data linkage

### Intervention

2.2

Supersaturated O_2_ (SSO_2_) therapy immediately following standard care primary PCI using exclusively radial artery access.

### Control

2.3

Control (sham) procedure in addition to standard care primary PCI.

### Primary objective

2.4

To assess within-participant changes in plasma concentration of N-terminal pro-B-type natriuretic peptide (NT-proBNP) measured at baseline (prior to primary PCI for acute anterior STEMI), and at 24 h, 2–5 days, and 3-months after primary PCI.

### Primary outcome

2.5

The plasma concentration of NT-proBNP at baseline (prior to primary PCI), and at 24 h, 2–5 days, and 3 months after primary PCI.

### Secondary objectives

2.6

The prespecified secondary objectives are listed in Table 1.

### Implementation

2.7

The study design involves prospective enrolment of patients with a diagnosis of acute anterior STEMI presenting within 6 h of symptom undergoing primary PCI. The protocol begins after primary PCI; the timepoint for randomization (time zero) is after primary PCI. The consent process will involve an initial witnessed verbal informed consent in the catheter laboratory during and/or at end of the primary PCI as felt to be appropriate by the attending clinician and before any change in the clinical workflow. Only after informed consent is given would any study related activities (including randomization) be undertaken.

Patients who fulfil the eligibility criteria and who have given witnessed informed verbal consent will be randomly assigned (2:1) to the intervention group or the control group.

The Patient Information Sheet and Informed Consent form for this study will be provided to patients and carers on the ward. If the patient is still happy to participate then written informed consent will be obtained. Study assessments will involve blood samples, cardiovascular magnetic resonance scans, health status questionnaires, and electronic case record linkage. If the patient is eligible to participate and agrees to have electronic health record linkage follow-up but no other assessments or procedures, then consent will be invited for electronic health record follow-up only (no visits).

### Setting

2.8

A tertiary care cardiothoracic center in the West of Scotland, United Kingdom. The NHS Golden Jubilee hospital provides primary PCI for approximately 650 patients per annum.

### Population

2.9

All-comers referred for primary PCI for acute anterior STEMI.

### Eligibility

2.10

The inclusion criteria are: age ≥18 years, ischemic time ≤ 6 h from symptom onset, acute anterior STEMI with infarct-related left anterior descending coronary artery TIMI flow grade 0–2 at initial angiography, infarct-related left anterior descending coronary artery TIMI flow grade 2–3 at the end of primary PCI, radial artery access and partial pressure of oxygen (PaO_2_) >80 mmHg (10.7 kPa).

The exclusion criteria are: proximal coronary artery stenosis that restricts blood flow with the SSO_2_ catheter in place, coronary dissection or perforation not treated with a stent at the completion of primary PCI, moderate or severe heart valve stenosis or insufficiency, pericardial disease, non-ischemic cardiomyopathy, known pregnancy, cardiogenic shock, contra-indication to systemic anticoagulation, acute mechanical complication (ventricular septal rupture, pseudoaneurysm, mitral regurgitation), hemoglobin <10 g/dL, major bleeding or major surgery within the past two months, contra-indication to CMR (severe claustrophobia, metallic foreign body) and/or a lack of witnessed verbal consent.

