### Enrolment, consent and randomization

2.11

Consecutive STEMI patients will be screened following referral to the CCU and on arrival at the hospital. Patients will be considered eligible according to the presence of inclusion criteria and absence of exclusion criteria. Screening will be performed by the attending cardiologist and/or research nurse; the final decision as to whether a patient is eligible to be included in the study will be made and documented by the treating cardiologist. Anterior STEMI patients will be assigned a screening log number. Baseline characteristics and the reason(s) for not being included will be recorded in a screening log database; no follow-up information will be recorded. Patients who are screened and who give informed consent will be recorded in an electronic case report form (eCRF). Patients who are initially eligible but who subsequently become ineligible (such as on angiographic grounds) will not proceed in the study and will become screen failures. Rarely, patients may be treatment allocation failures (such as for logistical reasons); their data will still be recorded in the eCRF.

Because of the need for emergency treatment, delays to obtain full written informed consent in the standard way is not appropriate. Based on experience in prior studies, initial verbal consent is proposed. This approach is in line with contemporary evidence [17], feedback from experts with lived experience and international practice guidelines [8,17]. Patients both fulfilling all inclusion criteria and no exclusion criteria and sufficiently able to understand information about the study (including the potential for benefit and known risks) would be eligible to participate and invited to give verbal informed consent by the attending cardiologist performing primary PCI.

Discussion of the study will take place in the presence of catheter laboratory staff and will cover all points listed in an approved Short Patient Information Sheet. If the patient agrees to participate, then a form to this effect will be signed by the attending interventionalist. Eligibility will be reviewed during primary PCI, reaffirmed at the end of the primary PCI and documented by a study clinician in the medical notes and/or eCRF.

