### Intervention group

2.15

The intervention includes SSO2 therapy given for 1 h via a biradial extracorporeal circuit in association with intravenous glycoprotein IIbIIIa inhibitor therapy with tirofiban for up to 12 h.

Contralateral radial access will be established and a 6 or 7F sheath placed for blood draw at a rate of 100 mL/min. Radial artery access will involve passing an 0.035″ (135 cm) to provide support for positioning a longer guiding sheath with a hydrophilic distal coating e.g. Destination, Terumo (6–7 French, 65 cm length), with the distal end positioned in the axillary artery, distal to the origin of the vertebral and mammary arteries.

Blood will pass through the Downstream® System Console (ZOLL Circulation Inc); hyperbaric blood will be returned via the contralateral radial artery into the left main coronary artery using a 5 French diagnostic catheter (Impulse, Boston Scientific). SSO_2_ therapy will continue for 60 min. Therapeutic anticoagulation will be maintained with a target ACT >250 s, measured every 15–20 min. Intravenous glycoprotein IIb/IIIa inhibitor therapy will be given during SSO2 therapy and continued for up to 12 h afterwards.

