## Discussion

3

This prospective, randomized, sham-controlled and blinded trial will, first, test the feasibility of an exclusively radial approach to both the delivery of primary PCI, in line with clinical guidelines, and thereafter SSO_2_ therapy. In other regards, combination therapy with SSO_2_ and an intravenous glycoprotein IIbIIIa inhibitor will be delivered according to existing regulatory approvals.

The study design includes several novel features. First, this study will provide novel information on the effects of SSO2 therapy in patients with anterior STEMI using radial artery access. This novel approach for SSO2 therapy has not been previously described. The design involves a 2:1 randomization with the aim of maximizing the information on feasibility, safety and efficacy of SSO2 biradial therapy coupled with intravenous glycoprotein IIbIIIa inhibitor therapy to mitigate thrombus formation, as compared to a sham control group. The study will primarily provide information on feasibility and safety using radial artery access. This is important because femoral artery access was used in prior studies [4,5] whereas radial artery access is now recommended in clinical practice guidelines [8].

Second, by targeting a high-risk subset, patients with anterior STEMI and ischemic times of <6 h, the study will also provide novel data on the effect of SSO_2_ therapy on multisystem biomarkers of cardiovascular function. Specifically, detailed insights into treatment effect will further be provided by intracoronary physiology, CMR imaging (including estimation of absolute myocardial blood flow (mL/min/g) at 3-months using stress/rest cardiovascular MRI) and blood biomarkers (to provide multisystem insights into the potential mechanisms of any differences in infarct characteristics and LV remodeling).

Third, NTproBNP is selected as the primary outcome measure of efficacy since NTproBNP is validated for cardiac prognosis and the blood sampling approach permits serial assessments during a 3-month follow-up period, providing data on the within-subject change over time and to mitigate for the possibility of missing data on the primary outcome, should the participant not attend for a follow-up visit.

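### Tirofiban is a fixed part of the SSO2 arm, but contra-indication to it is not an exclusion criterion

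*Protocol article*

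**What the plan says.** **The treatment.** Section 2.15 (Intervention group) describes one hour of SSO2 through a biradial circuit, "in association with intravenous glycoprotein IIbIIIa inhibitor therapy with tirofiban for up to 12 h". It goes on: "Intravenous glycoprotein IIb/IIIa inhibitor therapy will be given during SSO2 therapy and continued for up to 12 h afterwards". No exception or alternative is given for a patient who cannot have the drug. In the same section, "Therapeutic anticoagulation will be maintained with a target ACT >250 s". Section 2.16 gives controls saline in place of the inhibitor, so the inhibitor is a randomized component and not background care.

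**The criteria.** Section 2.10 (Eligibility) presents its list as the exclusion criteria. The items that bear on bleeding are "contra-indication to systemic anticoagulation", hemoglobin below 10 g/dL, and major bleeding or major surgery in the previous two months. Contra-indication to CMR is listed with examples. Contra-indication to a glycoprotein IIb/IIIa inhibitor is not listed.

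**How the criteria are used.** Section 2.11 states: "Patients will be considered eligible according to the presence of inclusion criteria and absence of exclusion criteria". On timing: "Eligibility will be reviewed during primary PCI, reaffirmed at the end of the primary PCI". The treating cardiologist makes and documents the final decision. Section 2.7 places randomization after primary PCI.

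**The drug's purpose.** The Discussion describes SSO2 as "coupled with intravenous glycoprotein IIbIIIa inhibitor therapy to mitigate thrombus formation", and says that SSO2 and "an intravenous glycoprotein IIbIIIa inhibitor will be delivered according to existing regulatory approvals".

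**The concern.** Eligibility for a randomized trial should mean that a patient can be given either arm. Here the experimental arm has three elements: SSO2, therapeutic heparin and tirofiban. The criteria ask whether the patient can have heparin but not whether the patient can have tirofiban.

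Two things are at stake.

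- **Patient safety.** A patient who should not have a platelet inhibitor could be assigned to one together with therapeutic anticoagulation and arterial access at both wrists. Freedom from major bleeding is part of the primary feasibility objective in section 1.1, so an avoidable bleed would also count against the technique under test.
- **Delivery of the assigned treatment.** If the problem is noticed only after allocation, the clinician must either give SSO2 without the agent included to limit thrombus or not give the assigned combination. Section 2.15 provides for neither. The departure can arise in the SSO2 arm only.

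No loss on the feasibility measure is claimed. Table 1 defines feasibility as completed SSO2 therapy, and nothing in the article says that omitting the inhibitor makes it incomplete.

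**Working it through.** The main check compares the sections. The arithmetic only shows that power is not the issue.

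**1. What is mandated and what is screened**

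| Element of the SSO2 arm | Where mandated | Contra-indication named in 2.10? |
|---|---|---|
| Heparin, ACT above 250 s | 2.12, 2.15 | Yes |
| Tirofiban, up to 12 h | 2.15 | No |
| CMR (both arms) | 2.19 | Yes |

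**2. Does the anticoagulation criterion cover the inhibitor?** Not by its wording. Section 2.12 names antiplatelet treatment and heparin anticoagulation as separate things, so clearing a patient for one does not clear the patient for the other.

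**3. Do the other exclusions cover it?** In part. Low hemoglobin and recent major bleeding or surgery remove some patients at risk from the inhibitor. They are not worded as contra-indication to the drug.

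**4. Chance of assignment.** With 2:1 allocation, an enrolled patient who cannot have the inhibitor is assigned to it with probability 2/3.

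**5. The plan's own figure.** Section 2.27 gives a minimum detectable difference of 0.85 SD with 51 complete participants, 80 % power and two-sided alpha 0.05. With 34 and 17 patients, a two-sample t-test (noncentral t, 49 df) gives 0.849 SD, and power at 0.85 SD is 0.801. The figure reproduces, and this concern does not affect it.

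**6. Effect of undelivered patients on power.** Inputs: 56 randomized 2:1, so 37 and 19; full follow-up; a true difference of 0.85 SD; k SSO2 patients in whom the combination is not delivered. The range k = 0 to 2 is an assumption. So is zero effect in each such patient, which is a worst case. The SD is held at 1.

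- Diluted difference: d = 0.85 × (37 − k)/37
- Noncentrality: d × √(37 × 19/56) = d × 3.543, with 54 df

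| k | d (SD) | Noncentrality | Power |
|---|---|---|---|
| 0 | 0.850 | 3.012 | 0.841 |
| 1 | 0.827 | 2.930 | 0.821 |
| 2 | 0.804 | 2.849 | 0.799 |

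The same calculation at 34 and 17, with d = 0.85 × (34 − k)/34 and 49 df, gives 0.801, 0.777 and 0.752. That version is harsher than the plan intends. The 56 − 51 = 5 extra patients are there partly to cover incomplete SSO2 therapy, so it charges for the loss twice.

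**The case against.** The case on the other side has five parts.

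- **A journal article condenses a fuller protocol**, and drug-level contra-indications are often left to that document. A longer list may exist. However, section 2.10 is worded as the list itself and goes down to severe claustrophobia and metallic foreign bodies. The point is that a stated criterion is too narrow for the treatment the same article mandates, not that detail is absent.
- **The Discussion says the combination follows existing regulatory approvals.** This makes it unlikely that a contra-indicated patient would actually be dosed. It concerns delivery and is not an eligibility criterion, so it does not keep the patient from being randomized.
- **The treating cardiologist makes a documented final decision**, after PCI complications are visible. This is a real safeguard. But the standard section 2.11 sets for that decision is the listed criteria, and unwritten discretion during an emergency under verbal consent is not a uniform check.
- **No condition is identified that contra-indicates tirofiban yet passes the existing exclusions.** This stands. The documents do not say what contra-indicates the drug, so the group cannot be sized and may be empty.
- **Existing provisions would absorb one or two such patients**: the sample size allowance, intention-to-treat with supporting as-treated analyses, and adjudicated bleeding events. This stands for the analysis, which is why power is not the ground. It does not answer the safety point.

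**Conclusion.** The concern holds. Followed as written, the criteria admit a patient who cannot have a drug that the SSO2 arm requires, and two-thirds of participants are assigned to that arm. The number affected is unknown, probably small and possibly zero. The existing exclusions and the cardiologist's decision reduce the risk but do not clearly remove the patient before randomization.

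There is no material loss of power: about 2 percentage points for one undelivered patient and 4 for two with all 56 followed up, on worst-case assumptions. The grounds are patient safety and delivery of the assigned combination. The change should be made because it closes a safety gap at almost no cost. No estimate or error rate in the plan is wrong on this account.

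The conclusion assumes that section 2.10 gives the criteria as applied. If the full protocol already lists the inhibitor, only the article needs correcting.

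**What to change.** In section 2.10, widen the existing anticoagulation exclusion so that it reads: contra-indication to systemic anticoagulation or to glycoprotein IIb/IIIa inhibitor therapy. Apply it to every patient, whichever arm follows, before randomization and at the end-of-PCI eligibility check that section 2.11 already requires. The investigators should decide which conditions count.

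The cost is a few words in one criterion and possibly a few fewer eligible patients. No new visit, test or analysis is needed.
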